#### Sample Size Adequacy:

The primary purpose of this pilot study is to develop the intervention and test feasibility/acceptability of interventions and research procedures as well as preliminary efficacy of the intervention. In the RCT, with follow-up data from 80 participants in intent to treat analyses (about 40 per condition, after the projected 20% attrition before month 3), we will have statistical power adequate (> = .80) to detect medium to large effects (Cohen’s d = .63 for continuous outcomes; 80% vs. 50% for dichotomous outcomes) with alpha of .05. The primary emphasis will be on estimating the effect for differences between conditions.

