**Methods:**

The proposed sample will be composed of 195 African American adults ages 18 + who live in Genesee County, Michigan. The study consists of two phases: the development phase and the randomized pilot study phase. The goal of the development phase (n = 95) is to explore how Family Health History toolkits can be modified to better serve the African American community using a community based participatory research approach and to create a culturally tailored family health history toolkit. In the pilot study phase, 100 participants will be randomized to the culturally tailored toolkit or the current standard Family Health History toolkit. Outcomes will include feasibility and acceptability of the intervention.

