The final part of the development phase is the open trial. This component consists of 15 AA adults that meet the aforementioned eligibility criteria. The open trial provides the opportunity to refine the created FHH toolkit. Study participants will fill out a session evaluation form asking them about their opinions of each session and how sessions could be made more helpful. Participants will also complete an intervention-specific End-of-Intervention Questionnaire, which addresses their perceptions of the helpfulness of each intervention component and their comfort with research procedures such as audiotaping and timing of the two FHH sessions. Participants will discuss their responses at an exit interview with the study principal investigator to aid in manual revisions.

The pilot study phase consists of the RCT. During the RCT, the intervention group will receive the AAFHHEP while the control group receives the EFHHEP. A total of 100 participants over the course of seven months will be recruited for this portion of the study. AAFHHEP participants will receive the intervention in two 60–90-minute sessions about 2 weeks apart. Session 1 focuses on understanding and reviewing FHH tools and its utility in risk assessment, including the AAFHHEP toolkit. Session 2 addresses family engagement strategies and provider engagement strategies. This session helps participants to develop personalized engagement plan resulting to actively engage family and their primary care providers (PCPs) utilizing the AAFHHEP toolkit. This toolkit will tailor messages around culture and spirituality that may preclude individuals from communicating. Participants will discuss what an FHH is, how choices affect health, how genetics affect health, what information to collect, how to engage family members in the conversation, how to organize FHH, and how to share information with their PCP. The feasibility and acceptability of AAFHHEP and EFHHEP will be assessed by examining rates of treatment attendance, rates of treatment completion (attending both scheduled group sessions) and drop-out, and scores on the End of Treatment Questionnaire, described below.

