### Analytic Plan

#### Data Analysis:

To achieve the goal of understanding the assessment and feasibility of this intervention, study recruitment and refusal rates, participants’ willingness to be randomized, follow-up rates, reliability, range of responses to study questionnaires, and success of the interventionist training program will be examined. The feasibility and acceptability of AAFHHEP and EFHHEP, as described previously, will be summarized with descriptive statistics. The acceptability of both interventions using data from CSQ-8-R satisfaction questionnaire and detailed exit interviews will be examined. Internal consistency and interrater reliability of fidelity scales will be computed

Primary RCT analyses will be intent-to-treat (using data from all enrollees as randomized) for the outcomes of FHH use (FHH discussed with a family and health care provider). Secondary dose- response analyses within intervention group evaluating effects of receiving 0, 1, or 2 intervention sessions will also be conducted. Longitudinal data will be analyzed using linear mixed effects or generalized linear mixed effects models with the appropriate error distribution (e.g., Binary) and covariance adjustment for the baseline version of the outcome where possible. These models can accommodate data missing at random and will be used to estimate the effect sizes at 3 and 6-month time points.

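### Both programmes are delivered in group sessions, but the stated power of at least .80 holds only if the 80 followed participants are independent, and the plan does not mention session group

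*Protocol article*

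**What the plan says.** **Delivery (Procedures).** The two programmes are assessed together: "The feasibility and acceptability of AAFHHEP and EFHHEP will be assessed by examining rates of treatment attendance", along with "rates of treatment completion (attending both scheduled group sessions) and drop-out". The schedule is spelled out for the tailored arm only: "AAFHHEP participants will receive the intervention in two 60–90-minute sessions about 2 weeks apart". That the control arm also meets in groups follows from the completion definition, which covers both programmes.

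**Size (abstract, Methods; Sample Size Adequacy).** "100 participants will be randomized to the culturally tailored toolkit or the current standard Family Health History toolkit". Power is computed on 80 followed participants, "about 40 per condition, after the projected 20% attrition before month 3". With alpha .05, the article says that "we will have statistical power adequate (> = .80) to detect medium to large effects", namely d = .63 for continuous outcomes and 80% vs 50% for binary ones. No group size, number of groups, ICC or design effect appears there.

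**Models (Data Analysis; Primary and Secondary Outcomes).** "Longitudinal data will be analyzed using linear mixed effects or generalized linear mixed effects models with the appropriate error distribution". Secondary outcomes use HLM. Baseline covariates are named; random effects and levels are not. Session group is neither included nor excluded.

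**The concern.** People who attend the same two sessions share a leader, a discussion and each other's influence. The sessions rehearse how to raise family health history with relatives and with a provider, and the main efficacy outcome of the randomised phase is whether those conversations then took place. Positive correlation within a session group is therefore plausible. Any such correlation reduces the information in 80 participants below that of 80 independent ones.

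Two things are at stake. The published power figure fixes enrolment and would overstate what the design can detect. Also, the between-arm effect sizes with 95% intervals are meant to inform a larger trial, and they would look more precise than they are if the analysis ignored session group.

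**Working it through.** **1. Reproduce the stated figure.** Inputs from Sample Size Adequacy: 40 per arm, d = .63 or .80 vs .50, alpha .05 (two-sided assumed, since this reproduces the figure).

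- Continuous: noncentrality = d × √(n/2) = .63 × √20 = 2.817. Power is Φ(2.817 − 1.96) = .804 by the normal approximation and .795 by the noncentral t with 78 df. At 80% power the detectable d by t is .634.
- Binary: mean proportion .65. Power = Φ{[.30 − 1.96 × √(2 × .65 × .35/40)] / √[(.80 × .20 + .50 × .50)/40]} = Φ{(.300 − .209)/.1012} = .816.
- Enrolment: 80/(1 − .20) = 100, as stated.

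The stated figure is therefore correct for independent participants. The design effect built into it is 1, with essentially no reserve.

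**2. Allow for session group.** Design effect DE = 1 + (m − 1) × ICC, and effective n per arm = 40/DE. Neither m (analysed participants per group) nor the ICC is given for the randomised phase, so both are assumptions. The only group size in the article is 8 to 12, for the development-phase groups. The main case is m = 8 (10 enrolled, 80% retained), that is 5 groups per arm and 10 − 2 = 8 group-level df.

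| ICC | DE | Effective n per arm | Power, d = .63 (78 df) | Power, d = .63 (8 df) | Power, 80% vs 50% | Detectable d (78 df) |
|---|---|---|---|---|---|---|
| 0 | 1.00 | 40.0 | .795 | .695 | .816 | .63 |
| .01 | 1.07 | 37.4 | .77 | .67 | .79 | .66 |
| .02 | 1.14 | 35.1 | .74 | .64 | .76 | .68 |
| .05 | 1.35 | 29.6 | .67 | .57 | .69 | .74 |
| .10 | 1.70 | 23.5 | .57 | .48 | .58 | .83 |

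The group-level df column is the stricter reading. It costs about ten points even at ICC 0, because there are only 10 groups.

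**3. Sensitivity to group size.** For 4 to 9.6 analysed per group (5 to 12 enrolled) with 78 df, power for d = .63 is about .76 to .78 at ICC .01, .64 to .74 at .05, and .53 to .68 at .10.

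**4. Consequence if the models carry no group term.** The interval should be √DE times as wide, and a nominal .05 test runs at about 2 × [1 − Φ(1.96/√DE)]. For m = 8:

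- ICC .02: √1.14 = 1.07; type I error .066
- ICC .05: √1.35 = 1.16; type I error .092
- ICC .10: √1.70 = 1.30; type I error .133

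This step is conditional. The article does not say that the group term is absent.

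**The case against.** **The models may already handle it.** A reader might infer that the planned analysis treats participants as independent. The article does not say so. It names mixed models and HLM, both of which can carry a random effect for session group, and it lists no random effects at all, not even one for the participant. A condensed article may leave that structure to the full protocol or analysis plan. This objection stands: intervals that are too narrow and an inflated type I error are possible consequences, not established ones. It does not rescue the power statement, because a group term makes the intervals honest but does not restore the lost information.

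**The shortfall is assumed.** Both group size and ICC are supplied here. With two sessions, and outcomes that occur later in each person's own family and clinic, the ICC may be small. At ICC .01 the loss is only one to three points. This stands as a limit on the size of the problem, not on its existence.

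**Baseline adjustment works the other way.** The plan adjusts for the baseline outcome where possible, and d = .63 takes no credit for that. If the baseline correlation were .5 (also an assumption), residual variance would fall to 1 − .25 = .75 and the effective d would be .63/√.75 = .727. With m = 8, power would then be about .85, .79 and .69 at ICC .02, .05 and .10 with 78 df, or .76, .69 and .59 with 8 df. The offset is real for continuous outcomes and does not carry over directly to the binary ones.

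**It is a pilot.** Feasibility and acceptability are the stated analytical goal, and the between-arm tests are exploratory. That lowers the severity. However, the same section lists preliminary efficacy as a purpose and puts its main emphasis on estimating the between-arm effect, so interval validity still matters.

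**Conclusion.** The point holds in a limited form. Both programmes are judged by group-session attendance, and the power of at least .80 is reached only with a design effect of 1. With 8 analysed per group and ICC .01 to .10, unadjusted power for d = .63 is about .77 to .57 and the detectable d is about .66 to .83. These figures rest on an assumed group size and ICC, and are worse with group-level df. Baseline adjustment could offset part or, at low ICC, all of the loss for continuous outcomes.

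Two stronger readings are not supported. The first is that the planned models ignore clustering; the article leaves this open. The second is that the month-6 comparison is quantifiably underpowered. The attrition allowance does refer to "after the projected 20% attrition before month 3", but the article gives no later loss rate, and the mixed models still use month-3 data from participants lost afterwards.

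For a pilot with exploratory between-arm tests this is a correction worth making, not a flaw that invalidates the study.

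**What to change.** 1. Record a session-group identifier for every participant in both arms. This is easy to do prospectively and may be hard to reconstruct later.
2. Include, or confirm, a random intercept for session group within arm in the between-arm linear and generalised linear mixed models and the HLM analyses, with a small-sample df correction (for example Kenward-Roger for the linear models).
3. Restate Sample Size Adequacy with the planned group size, an assumed ICC range and the resulting detectable effect. If baseline adjustment is credited, state the assumed baseline correlation. With 8 analysed per group, ICC .01 to .10 and no such credit, the detectable d would read about .66 to .83 in place of .63.

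The cost is one data field, one model term, wider intervals and a less favourable stated detectable effect. Enrolment need not rise, since the emphasis is on estimation. An estimate of the session-group ICC, though imprecise, would also be useful for planning the larger trial.

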## Discussion

The Family Health Histories Study seeks to create a culturally appropriate FHH tool to inform AAs about their health and the health of their families with the intention of increasing preventative behaviors. Preventative behaviors will lead to improved health and reduce incidence of disease and illness. This is the first study to co-create and co-design and AA specific FHH tool. The community-engaged study design allows for incorporation of opinions from those who will benefit from the FHH directly. The setting of the study in Genesee county, MI is especially meaningful given the historic mistreatment of the county’s population, including the ongoing Flint water crisis. The inclusion of focus groups, workshops, and an open trial prior to conducting an RCT creates iterative opportunities to identify issues, implement changes, and improve the tailored FHH tool to make it more culturally relevant. Conducting follow ups with participants of the RCT at three and six months allows for assessment of immediate and longer-term outcomes. Assessments also include potential mediators of intervention effects, including health literacy and health communication, to inform a subsequent fully-powered trial.

Results from this study can inform how primary care provider’s structure their family health history forms, particularly when working with marginalized communities and given health literacy concerns. Meaningful FHH discussions between patients and providers can further contribute to addressing HD and increasing preventative health behaviors. Future interventions guided by this research include expanding the intervention guide to geographies beyond Genesee County, MI. Geographical areas with a large AA community will provide a greater understanding of the generalizability of the culturally tailored tool.

## Conclusion

HD are caused by a multitude of factors and, as a result, require interventions on multiple levels. While efforts are being made to mitigate these effects, continued research is needed to explore additional mechanisms through which HD operate and to identify ways to combat them. This study will create a culturally tailored AA FHH tool, lead to subsequent testing of its effects on healthcare utilization and outcomes, with the goal of reducing HD.

## Figures and Tables

**Figure 1 F1:**
[figure not shown]
Study Model

**Figure 2 F2:**

Study Phases and Components

## Abbreviations

AA: African American
HD: Health Disparities
AAFHHEP: African American Family Health History Education Program
EFHHEP: Existing, non-tailored Family Health History Education Program
